## Abstract

**Background:**

The human microbiota has a broad range of functions contributing to metabolic processes and the activities of our immune system. Its influence on health, well-being and chronic diseases are discussed in various studies. The intestinal microbiota and the mucosal integrity are influenced by diet, environment and other lifestyle factors, including physical activity. There are correlations between cardiorespiratory fitness and important markers of intestinal health. However, data linking endurance exercise to microbiota composition are sparse. Many endurance athletes take probiotics to reduce gastrointestinal symptoms linked to exercise or immunosuppression, but the longitudinal data is insufficient.

This randomised, controlled cross-over pilot study will examine the impact of specific endurance training and probiotic supplementation on the intestinal microbiota and mucosa in healthy, athletic students.

**Objective:**

The aim of this pilot study is to elucidate the impact of physical activity on the intestinal microbiota and mucosa with regard to the effects of a probiotic supplementation.

**Methods:**

In this pilot study, thirty non-specifically trained student athletes will participate in an intervention consisting of a two-week rest (baseline) period, a four-week exercise programme and a four-week probiotic intervention using SymbioLactComp®. The exercise programme consists of three 60-min running workouts per week at 70–85% of the peak heart rate (HRpeak). Primary endpoint of this pilot study is the feasibility and practicality of the intervention as well as a sample size estimation. Furthermore, anthropometric measurements and information on nutrition and lifestyle will be obtained. The peak oxygen uptake (VO_2_peak) and peak heart rate (HRpeak) (determined during a shuttle run test) as well as selected blood and saliva parameters (haemogram, cytokines) will be evaluated. Changes to the intestinal microbiota will be analysed by stool diagnostics (KyberKompaktPRO®, KyberPlus®). The potential changes may include microbiota composition, bacterial metabolites and mucosa- and immune markers.

**Conclusion:**

Results will be used for the design of a main randomised controlled trial with a larger collective based on feasibility, validity and sample size estimation as well as the potential effects of endurance exercise on intestinal microbiota and mucosa. Evidence-based information of an exercise-altered microbiota could be of importance for the prevention and therapy of intestinal or immune disorders.

**Trial registration:**

German Clinical Trials Register: DRKS00011108. Retrospectively registered on 28 November 2016.

**Electronic supplementary material:**

The online version of this article (10.1186/s40814-019-0459-9) contains supplementary material, which is available to authorized users.

## Introduction

The intestinal microbiota composition plays a significant role in metabolism and immunity [1, 2]. Certain species and their associated metabolic products influence physiological homeostasis. For instance, the microbiota is involved in the degradation of food and the synthesis of vitamins, bioactive compounds and hormones such as serotonin. It further plays a role in the training of the immune system, pathogen defence and proliferation of intestinal cells [3, 4]. There is no recognised definition of an intact microbiota. However, the following aspects are believed to play an essential role: an enriched bacterial diversity (alpha diversity), a balanced *Firmicutes*/*Bacteroidetes* ratio, an intact mucus layer and an abundance of certain species (e.g. *Akkermansia muciniphila* and *Faecalibacterium prausnitzii*) [5–9]. An altered microbiota contributes to the pathogenesis of diseases such as metabolic or (auto)-immune diseases [10–13]. Recent studies have highlighted that environment and lifestyle factors affect the microbiota composition and its metabolic capacity [14, 15]. There is a growing body of evidence indicating that physical activity is linked to specific markers of intestinal health [16–19].

Several studies determined a higher species richness (*α* diversity) in elite athletes and individuals with higher cardiorespiratory fitness (VO_2_peak) or higher training frequency than those with a sedentary lifestyle or lower fitness level [16, 17, 20].

Furthermore, an increase in number of the two commensal species *Akkermansia muciniphila* and *Faecalibacterium prausnitzii* was observed in athletes and highly active individuals [17, 18, 20]. This was related to a higher concentration of the health-promoting bacterial metabolite butyrate [18, 20].

Some professional athletes suffer from immunosuppression or gastrointestinal symptoms, including abdominal pain, diarrhoea or leaky gut syndrome. This is because excessive exercise reduces intestinal blood flow due to increased circulation in the strained muscles and heart. This may lead to microbial imbalances and mucosa disruption [19, 21–24]. An increased permeability of the intestinal mucosa and epithelium (intestinal barrier) has been associated with bacterial/pathogen translocation to extraintestinal organs manifesting as intestinal or systemic inflammation [25–27].

Many athletes use probiotics to enhance barrier integrity and to improve gastrointestinal symptoms. The consumption of a probiotic supplement may induce immune processes, including the synthesis of cytokines and immunoglobulins, thereby contributing to the host’s health [28–30]. Previous research with trained athletes revealed the beneficial effects of probiotic intake on zonulin, a marker of mucosal integrity and several cytokines. Interferon-gamma, tumour necrosis factor-alpha and interleukins were all improved [19, 29, 31–33].

Regular moderate exercise is well-known for its anti-inflammatory effects, but diet may be a confounding factor in exercise-related impacts on the gastrointestinal system [17, 18]. Data that determines causality between microbiota composition, mucosa permeability and moderate endurance training is sparse. Longitudinal studies are needed to determine how the intestinal microbiota and mucosa as well as immune markers and cytokines vary with exercise as compared to probiotic supplementation. A combination of exercise and probiotics may be a new method for the prevention and therapy of intestinal or immune-related diseases [34–36].

### Research hypothesis

We hypothesise that a training intervention with regular running exercises may alter microbiota composition in healthy adults. Participants receiving the intervention might further show higher rates of selected markers of intestinal health such as *Akkermansia muciniphila, Faecalibacterium prausnitzii, Bifidobacterium* spp. and lower rates of intestinal immune markers, e.g. zonulin, alpha-1-antitrypsin or secretory immunoglobulin A (sIgA).

### Aims and objectives

Primary outcomes of this randomised, controlled, cross-over pilot trial are the feasibility and practicality of the intervention, the validity of the study design and the provision of a reliable estimate for sample size calculation. To assess the practicality of the intervention, the duration (60 min), frequency (three times per week) and intensity (70–80% HRpeak) of the exercise programme will be considered as well as the adherence to the daily probiotic supplementation. The validity of the study design will be assessed with regard to the collection and immediate shipping of faecal samples. A further assessment will be made considering the time commitment for participants to complete endurance training, anthropometric testing, faecal samples and food diaries. In order to evaluate the efficacy of the intervention, the influence of moderate endurance training compared to probiotic supplementation (SymbioLactComp®) on the intestinal microbiota composition and barrier function (selected mucosal and immune parameters) as well as on selected blood and saliva biomarkers (haemogram, selected cytokines) in healthy student athletes will be examined.

## Methods

### Pilot trial design, study setting and ethics

This randomised controlled pilot cross-over trial is conducted at the German Sport University Cologne in cooperation with the MVZ Institute of Microecology GmbH. Data will be collected through bachelor endurance courses at the German Sport University Cologne (Cologne, Germany).

The study was approved by the Ethics Committee of the German Sport University Cologne (No. 136/2016). A schematic of the study design is given in more detail (see Additional file 1). To ensure all necessary aspects were addressed in the study protocol, the Standard Protocol Items: Recommendations for Interventional Trials (SPIRIT) checklist was adhered [37, 38] (Additional file 2).

### Experimental design

Participants will receive a 12-week intervention programme including a 2-week rest period, a 4-week endurance training programme and a 4-week probiotic intervention with SymbioLactComp®. Subjects will not perform endurance sports or take probiotics during the rest period but will participate in the university courses during the programme (e.g. gymnastics, volleyball, tennis).

#### Exercise intervention

Exercise intensity will be calculated based on the HRpeak determined during a shuttle run test performed at the outset of the study. The training goal is a 10-km run in 50 min (males) or 55 min (female). The intensity of exercises will increase from 70% to 85% of the HRpeak to improve the subject’s basic endurance [39]. The three 60-min running sessions per week will consist of extensive and intensive continuous methods, interval training and stretching [39]. The exercises will be performed in groups and supervised by a sports scientist. Ratings of perceived exertion will be checked using a Borg Scale; the heart rate will be measured using a pulse monitor and belt from Polar® (Polar® Typ FT1). Participants will keep a training diary to log the completion of exercises. A training plan is shown in more detail in the appendix (see Additional file 3).

#### Probiotic intervention

The probiotic period involves supplementation with the probiotic SymbioLactComp® (SymbioPharm GmbH, Herborn, Germany). SymbioLactComp® contains different lactic acid bacteria (*Lactobacillus paracasei*, *Lactobacillus acidophilus*, *Lactococcus lactis* and *Bifidobacterium animalis* subsp. *lactis*) as well as 30 μg of biotin. The total bacteria count of one sachet (2 g) is ≥ 1 × 10^9^ KBE/g. One sachet will be mixed with water and taken daily at breakfast.

### Pre-experimental procedures

#### Anthropometry

Anthropometric characteristics, arterial blood pressure and body composition will be measured. Body weight will be determined barefoot and in light clothes using a calibrated digital scale (Seca® Typ 771). Body height will be measured by a wall-mounted measuring tape (Seca® Typ 225). Body mass index will be calculated by the World Health Organization’s specifications (BMI = body weight (kg)/body size (m)^2^) [40]. Systolic and diastolic blood pressures will be measured three times after 5 min of sitting calmly using a digital blood pressure monitor (OMRON® Typ M5-1). Body fat and muscle mass will be estimated using bioelectric impedance analysis (EGOFIT GmbH, Eggstätt, Germany).

Furthermore, information on the participant’s personal history and lifestyle including physical activity levels will be collected prior to the start of the trial (T0) using a modified questionnaire (International Physical Activity Questionnaire; [41].

#### Cardiorespiratory fitness

A standardised multistage 20-m shuttle run test will be performed at the outset of the study to calculate HRpeak and the VO_2_peak as an indicator of the participants’ cardiorespiratory fitness [42].

The test will be executed by running back and forth on a 20-m course. A sound signal emitted from a prerecorded tape will set the pace. The starting speed is 8.5 km/h and will be increased by 0.5 km/h each minute, representing a stage. Participants must touch the 20-m line even after the acoustic signal. If the participant is not able to follow the pace, the test is finished. The last stage number will be used to determine the HRpeak by a pulse monitor and belt (Polar® Typ FT1) as well as the VO_2_peak. VO_2_peak will be calculated according to Léger and Lambert [42]: VO_2_max (mL kg^−1^ min^−1^) = − 24.4 + 6.0 × “maximal shuttle run speed”/km h^−1^. The shuttle run test will be repeated after the 4-week training period in order to define the potential performance improvement.

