### Sample size

It is estimated that a sample size of a minimum of 30 participants is required in order to provide a pooled standard deviation that provides enough precision for the development of a future trial [46, 47].

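### VO2peak scored by last stage number moves only in steps of 3.0 mL/kg/min, which adds avoidable noise to individual pre-post change; recording completed shuttles would remove most of it

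*Protocol article*

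**What the plan says.** All of the scoring is in the Protocol article, Methods, section Cardiorespiratory fitness.

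- Course: "The test will be executed by running back and forth on a 20-m course".
- Stages: "The starting speed is 8.5 km/h and will be increased by 0.5 km/h each minute, representing a stage".
- Scoring unit: "The last stage number will be used to determine the HRpeak by a pulse monitor and belt (Polar® Typ FT1) as well as the VO_2_peak".
- Prediction equation: a minus sign followed by "24.4 + 6.0 × “maximal shuttle run speed”/km h^−1", that is, an intercept of −24.4 and a slope of 6.0 mL/kg/min per km/h.
- Purpose of the second test: "The shuttle run test will be repeated after the 4-week training period in order to define the potential performance improvement".

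The section mentions no count of shuttles and no credit for part of a stage. The article gives no expected gain, no SD of change and no test-retest error for VO2peak. On the standing of the measure, Aims and objectives says: "Primary outcomes of this randomised, controlled, cross-over pilot trial are the feasibility and practicality of the intervention". The same section adds the validity of the design and an estimate for sample size calculation. VO2peak is not among the primary outcomes.

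**The concern.** The second test is there to measure improvement within a person over four weeks, so what matters is how finely change can be read. A stage lasts a full minute. A student who stops on the first shuttle of a stage before training and on the last shuttle of that stage afterwards has the same score twice. A student who gains one shuttle across a stage border is credited with a full step. Two people with nearly the same improvement can therefore differ by a whole step in the data.

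At stake are the precision of the mean change in VO2peak, the SD of change that the pilot would pass on to a later trial if VO2peak were carried forward, and any exploratory correlation or regression that uses fitness change.

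**Working it through.** **Plan's own figure.** There is none to reproduce: the article states no step size, resolution or expected gain for VO2peak.

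**Inputs from Cardiorespiratory fitness.** Slope 6.0 mL/kg/min per km/h; stage increment 0.5 km/h; start 8.5 km/h; stage length 1 minute; course 20 m. **Input from Sample size:** "It is estimated that a sample size of a minimum of 30 participants is required".

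**1. Step.** 6.0 × 0.5 = 3.0 mL/kg/min. The score at 12.0 km/h is −24.4 + 6.0 × 12.0 = 47.6, and the next possible value is 50.6. The step is 3.0 / 47.6 = 6.3% of the score at that speed. It is the same whether last stage means last reached or last completed, and a consistent choice cancels from the change.

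**2. What happens to a gain below one step.** Assume starting points spread evenly within a stage and no retest error. A gain *g* below 3.0 is then recorded as 0 with probability 1 − *g*/3.0 and as 3.0 otherwise.

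| Assumed true gain (mL/kg/min) | Recorded as 0 |
|---|---|
| 1.0 | 67% |
| 1.5 | 50% |
| 2.0 | 33% |
| 2.5 | 17% |
| 3.0 or more | 0% |

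**3. Group mean.** The expected recorded gain is 3.0 × *g*/3.0 = *g*, so the mean is preserved. A simulation with baseline VO2peak of mean 50 and SD 5, and gains of mean 1 to 4 and SD 0.5 to 2 (all assumed), returned the true mean gain to within about 0.01.

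**4. Added variance.** One rounding to a step of 3.0 has variance 3.0²/12 = 0.75. Two tests give 2 × 0.75 = 1.5. Relative to the variance of change without rounding:

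| Assumed SD of change | Variance | Increase |
|---|---|---|
| 1.5 | 2.25 | 1.5 / 2.25 = 67% |
| 2.5 | 6.25 | 1.5 / 6.25 = 24% |
| 3 | 9 | 1.5 / 9 = 17% |
| 4 | 16 | 1.5 / 16 = 9% |

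The simulation agrees where gains vary enough between people: an SD of gain of 1 became about 1.6 (1.6² − 1² = 1.56), and 2 became 2.34 (2.34² − 2² = 1.48). If gains hardly vary between people, the added variance depends on where the mean gain falls relative to the step, and 1.5 is only an average.

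**5. Effect on precision with 30 participants.** The 95% half-width is 1.96 × SD / √30. For an SD of gain of 1 it goes from 0.36 to 0.57. For an SD of 2 it goes from 0.72 to 0.84.

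**6. Effect on a correlation with fitness change.** The shrinkage factor is 1/√(1 + increase): 1/√1.67 = 0.77 at SD 1.5, 1/√1.24 = 0.90 at 2.5, 1/√1.17 = 0.92 at 3, and 1/√1.09 = 0.96 at 4.

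**7. Resolution with shuttles.** Shuttles per stage at *v* km/h are *v* × 1000 / 60 / 20: 7.1 at 8.5, 10.0 at 12.0 and 12.5 at 15.0 km/h (the upper speed is an assumption). One shuttle then corresponds to 3.0 / 7.1 = 0.42, 0.30 and 0.24 mL/kg/min, so the reading is 7 to 12.5 times finer. Converting a shuttle to VO2peak in this way assumes linearity within a stage. The shuttle count itself needs no such assumption.

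**The case against.** A reader might infer that many real gains over the four weeks will be recorded as zero. The documents do not support this. The article gives no expected gain, and the participants are described both as athletic and as not specifically trained, so small gains are a guess. In the simulation, positive gains recorded as zero were 41–66% at a mean gain of 1, 30–34% at 2, 7–19% at 3 and 0–11% at 4. Nor are gains lost on average, because the zeros are offset by small gains recorded as 3.0.

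The variance figures depend on SDs that the article does not give. A maximal field test has day-to-day error, which enlarges the SD of change and makes the rounding matter less, as the rows for SD 3 and 4 show. A finer reading is also not the same as a more precise measurement, since retest error stays.

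The uses are limited. VO2peak is not primary, no section says that its SD will size the main trial, and Statistical analysis offers correlations only as a possibility, without naming variables, and treats hypothesis tests as exploratory. Training intensity is set from HRpeak, which the VO2peak step does not touch. All of this stands and keeps the point small.

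Two further criticisms might be read into the same section, and neither holds. HRpeak is not calculated from a stage number: the text has it measured by monitor and belt. The sentence "Participants must touch the 20-m line even after the acoustic signal" can simply mean that a late runner must still reach the line, and the number of late touches that ends the test is operating detail that a condensed article may leave to the full protocol.

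What the objection does not remove is the step. The article itself names the stage number as the scoring unit and the repeat test as the measure of improvement.

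**Conclusion.** The point holds in a limited form. As written, VO2peak changes only in steps of 3.0 mL/kg/min, and an individual gain below that is recorded as 0 or 3.0. This follows from the article's own figures and needs no assumption beyond taking the stage score literally.

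The group mean change is roughly unbiased. The cost is about 1.5 of extra variance in individual change, between +67% and +9% for assumed SDs of change from 1.5 to 4, with wider intervals and weaker exploratory correlations. How many participants would be scored as unchanged cannot be said without an expected gain. For a non-primary measure in a feasibility pilot the impact is minor, but the loss is avoidable, and the shuttle count cannot be recovered later from the stage number.

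**What to change.** At both shuttle run tests, record the number of completed shuttles, or the total distance, and name that as the measure of performance improvement. Keep the stage-based VO2peak for comparison with other studies. If a finer VO2peak is wanted, report an interpolated value as a labelled supplement and state that linear interpolation within a stage is an assumption, since the printed equation is in terms of speed.

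The cost is one additional count per participant at each of the two tests (2 × 30 = 60 counts at the minimum sample size) and a short change of wording. The test itself does not change.

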### Randomisation

Participants will be randomised in a 1:1 ratio and allocated to group one (endurance-probiotics) or group two (probiotics-endurance) via block randomisation by the study director [48]. Exclusion criteria will be injuries; diseases (e.g. inflammatory bowel diseases), an antibiotic therapy just before or during the intervention; and continuing gastrointestinal disturbances based on probiotic intake. Subjects who meet the inclusion criteria will obtain detailed information about the trial and will give written informed consent before starting the study.

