### Statistical analysis

This pilot study intends to examine the confidence interval estimation and feasibility of the presented approach (physical activity and probiotic supplementation) [49, 50]. Attendance and retention rates will be assessed to calculate adherence. Attendance rate will be analysed by dividing the mean value for the number of participants present by the number of sessions offered during the four-week exercise period and the four-week probiotic intervention. The retention rate will be analysed by the percentage of participants completing all sessions of the endurance training (twelve in total), shuttle run test (two in total), nutrition questionnaire (four in total), blood/saliva measurement (four in total) and stool diagnostics (four in total) present in each step of the study. A retention rate of > 80% will be considered as feasible to conduct a future randomised controlled trial. Hypothesis testing and results of regression modelling will be considered entirely exploratory in nature and interpreted with caution. Our trial is mainly conducted in preparation for a future definitive randomised controlled trial to assess the efficacy of the intervention/study design [51]. All data will be entered into the database management software and analysed by the SPSS Version 25.0 (SPSS Inc., Chicago, IL, USA). The Shapiro-Wilk test will be used for variable normal distribution and the usual descriptive statistics for background information and mean values with a 95% confidence interval. Data will be used for sample size estimation and to determine the most appropriate outcome measure for the main study. Descriptive statistics and confidence intervals will also be calculated to examine the trends in the analysed parameters. This information will help to identify which parameters to focus on in future trials. Depending on the normality of the underlying data, parametric or non-parametric (e.g. unpaired *t* test/Mann-Whitney *U* test) tests will be carried out. Furthermore, a paired *t* test/Wilcoxon test might be computed for the longitudinal comparison (T0–T3). Bivariate correlation analyses might be assessed by the Spearman/Pearson correlation coefficient. Multivariate analyses with linear or logistic regressions might be performed to explore potential effects of the intervention and further potential covariates and cofactors. Moreover, multiple regression models might be used if multiple variables are predictive. The level of statistical significance is *p* < 0.05.

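### With one shuttle run at study start and one after training, the change in VO2peak does not isolate the training effect in the probiotics-endurance sequence

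*Protocol article*

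**What the plan says.** The first test is described in the Cardiorespiratory fitness section of the protocol article, under the pre-experimental procedures: "A standardised multistage 20-m shuttle run test will be performed at the outset of the study to calculate HRpeak and the VO_2_peak". The Exercise intervention section gives the same timing: "Exercise intensity will be calculated based on the HRpeak determined during a shuttle run test performed at the outset of the study". Neither section distinguishes between the two sequences.

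One repeat is planned, with a stated purpose: "The shuttle run test will be repeated after the 4-week training period in order to define the potential performance improvement". The Statistical analysis section, in listing what counts towards retention, confirms the number: "shuttle run test (two in total").

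The Randomisation section sets up the cross-over: "Participants will be randomised in a 1:1 ratio and allocated to group one (endurance-probiotics) or group two (probiotics-endurance"). The Experimental design section gives the period lengths: "12-week intervention programme including a 2-week rest period, a 4-week endurance training programme and a 4-week probiotic intervention". On other activity it says: "Subjects will not perform endurance sports or take probiotics during the rest period but will participate in the university courses during the programme".

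**The concern.** A pre-post change measures what happened between the two tests. If the first test is tied to the calendar (study start) and the second to the participant's own training block, the two enclose the same exposure only when everyone trains in the same period. In a cross-over they do not.

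In endurance-probiotics the tests enclose the training block and, at most, the rest period before it. In probiotics-endurance they also enclose the whole probiotic block. The one quantity meant to show the performance improvement thus has a different content in each randomised sequence.

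Three uses are at stake. A mean change over all participants would not be a clean training effect. A difference between sequences could arise from test timing alone. If the change in VO2peak were entered as a covariate in the exploratory regressions, its meaning would depend on sequence. The pilot is also meant to judge the study design for a main trial, so an uncorrected schedule could be carried forward.

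**Working it through.** **Inputs, all from the protocol article**
- First test: study start, all participants (Cardiorespiratory fitness; Exercise intervention).
- Second test: after the training block (Cardiorespiratory fitness).
- Rest 2 weeks, training 4 weeks, probiotic 4 weeks, stated total 12 weeks (Experimental design).
- Allocation 1:1 (Randomisation), minimum of 30 participants (Sample size), hence about 15 per sequence.
- Stage increment 0.5 km/h, and a slope of 6.0 mL/kg/min per km/h in the VO2 equation (Cardiorespiratory fitness).

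**Step 1: the plan's own count.** One test at the start + one after training = 2. This matches the two in the Statistical analysis section, so the schedule leaves no room for a further test just before training.

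**Step 2: unlisted time.** 2 + 4 + 4 = 10 weeks are listed and 12 are stated, which leaves 12 − 10 = 2 weeks that the text does not place.

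**Step 3: interval between tests.** Let r be the rest weeks inside the interval (0 if the first test follows the rest period, 2 if it precedes it). Let g be the weeks between the two blocks (0, or 2 if the unlisted weeks fall there).
- Endurance-probiotics: r + 4
- Probiotics-endurance: r + 4 + g + 4

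| r | g | Endurance-probiotics (weeks) | Probiotics-endurance (weeks) | Difference (weeks) | Training share of interval |
|---|---|---|---|---|---|
| 0 | 0 | 4 | 8 | 4 | 100% vs 50% |
| 0 | 2 | 4 | 10 | 6 | 100% vs 40% |
| 2 | 0 | 6 | 10 | 4 | 67% vs 40% |
| 2 | 2 | 6 | 12 | 6 | 67% vs 33% |

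The text does not say which row applies. In every row the second sequence's interval is 4 to 6 weeks longer, and training fills at most half of it. If the unlisted weeks fall elsewhere, they lengthen both intervals equally or neither, and the difference stays at 4 weeks.

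**Step 4: how a shift before training would enter the result.** This is an illustration only; the protocol gives no figure for such a shift. One stage of the test equals 0.5 × 6.0 = 3.0 mL/kg/min. If fitness in probiotics-endurance moved by an average of one stage before training began, that sequence's mean change would be off by the full 3.0. The pooled mean over 30 would be off by 15 × 3.0 / 30 = 1.5. With half a stage the figures are 1.5 and 0.75. The sign is open: fitness could fall without endurance training, or rise, because the bar on endurance sport is stated for the rest period only and university sport courses continue.

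**Step 5: age of the HRpeak value.** The same timing means that the HRpeak used for training intensity is at least 4 weeks old when group two starts to train (the length of the probiotic block).

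**The case against.** The strongest reply is that little depends on this measure. Change in VO2peak is neither a primary outcome nor among the efficacy targets in Aims and objectives, which are the microbiota, barrier markers and blood and saliva markers. The Statistical analysis section names no pooled comparison of fitness and no test of sequence on fitness. Its correlations and regressions are optional, and it treats hypothesis tests and models as exploratory. This stands, and it limits the point to a secondary measure. It does not remove it, because the article itself assigns the repeat test the job of defining the improvement.

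A second reply is that a test at study start has its own value. It gives a VO2peak before any treatment in both groups, and the Introduction links cardiorespiratory fitness to bacterial diversity. That also stands, and it is the real cost of moving the test.

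The schematic and training plan in the additional files are not shown. A third test there would contradict the count of two in the main text, so they could not settle the matter by themselves.

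A reader might infer several stronger things that the document does not support:
- **That group two's change says nothing about training.** It contains the training effect; it does not separate it from the rest.
- **That the shuttle run is the only objective check on the exercise.** The Exercise intervention section also provides supervision, heart-rate monitoring and a 10-km time goal. The shuttle run is the only repeated fitness test described, which is a narrower statement.
- **That group two's gain is understated by some known amount.** No passage supports a size or a direction.
- **That the first test certainly precedes the rest period.** The text does not say.
- **That training intensity in group two is wrongly set.** Nothing shows that HRpeak would shift over the interval. Only the age of the value follows from the text.

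**Conclusion.** The point holds on the article's own schedule. In probiotics-endurance, the change in VO2peak between the two planned tests does not isolate the training effect, because the whole probiotic block lies between them. This affects about 15 of 30 participants, assuming the minimum sample is split evenly.

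The conclusion does not depend on where the first test falls relative to the rest period, or on where the two unlisted weeks fall; these alter only the lengths. The size of any bias cannot be derived from the document, and its direction is unknown. What can be said is that the two sequences' changes are neither comparable nor poolable as a training effect.

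The consequence is limited to a secondary, exploratory measure and to any use of it as a covariate. Recruitment, adherence, retention and the sample-size aim are unaffected. It is worth correcting because the correction is cheap.

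**What to change.** Take the first test of the pair just before each participant's own training block, after that time point's stool, blood and saliva samples have been collected. The interval is then about 4 weeks in both sequences, all of it training, and each participant still has two tests. State in the text where this test falls relative to the rest period.

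The cost should be named. Group two's VO2peak would then be measured after randomisation and after the probiotic. The randomised groups could not be compared on baseline fitness, and VO2peak could not serve as a baseline covariate. If the sponsor wants to keep the test at study start as well, group two has three tests, and the count in the Statistical analysis section, which feeds the retention rate, must be changed to match.

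If the test dates stay as they are, report the change separately by sequence with the interval stated. Say that neither group two's change nor a pooled change is to be interpreted as the training effect. This costs only wording.

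The article should also acknowledge that group two's HRpeak is at least 4 weeks old when its training starts. How training intensity is set is for the sponsor to decide.
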